## Discussion

This is one of the first clinical trials in psychiatry to use a priori stratification of patients based on inflammatory biomarkers to test the efficacy of an anti-inflammatory intervention. There are, however, several previous studies that have used enrichment strategies to test the antidepressant effects of anti-inflammatories in a subgroup of inflammatory depression [49, 50]. These studies have, however, not included a non-inflammatory reference group, which might be necessary to answer the important clinical question if a biomarker can be used a priori to predict treatment response in a given depressed individual. Our study will be able to inform not only about the efficacy of this particular intervention (EPA) in a specific clinical population (inflammatory depression), but also test the feasibility of this novel match-mismatch study design in clinical psychiatric research.

The traditional RCT design is considered the gold standard for evidence-based medicine but has also been criticized for being expensive, biased in design, recruitment and data analysis, as well as testing general, broad feasibility rather than if the treatment is effective in certain, selected cases [51, 52]. Recent recommendations have been made to stratify subjects based on an a priori hypothesis, when assessing if a treatment might be efficacious in a certain subpopulation, as in this case of inflammatory depression [19]. Rapaport and colleagues found a benefit of using a combination of inflammatory markers to predict antidepressant treatment response to n-3 fatty acids [18]. Among individual inflammatory markers they found hs-CRP to be one of the strongest predictors of treatment response at baseline [18]. Even though serum hs-CRP is an established marker of inflammation both peripherally and centrally, levels may be affected by a variety of factors such as overweight and old age, as well as infections, or undiagnosed acute or chronic inflammatory processes. This was taken into consideration when designing the study, specifically when defining our exclusion criteria. Since all participants in this match-mismatch study receive the same active treatment and instead are stratified based on levels of inflammation, potential confounders such as off-target effects and adverse events might have less of an impact. The design makes it possible, in comparison to traditional RCTs, to discern whether the treatment is broadly effective in all patients or more effective in a smaller group with high inflammation [17].

For this study, we chose an approach where the primary outcome measure is an expert assessment scale, the HAM-D-17. We decided, however, to also add several secondary outcome measures including self-ratings, objective measures of cognitive performance and blood biomarkers. Our primary outcome measure, change in the HAM-D-17 score, was chosen mainly since it would facilitate comparison of our results with previous studies. The HAM-D-17 has been commonly used in clinical work and psychiatric research since its introduction in 1960 [53]. It has long been considered the gold standard but it has also been criticized with regards to poor inter-rater and retest reliability [54]. The HAM-D might also have other shortcomings including that several items measure de facto antidepressant side effects (*e.g.* insomnia, weight loss) which, some have argued, should result in the selection of shorter, unidimensional rating scales in future clinical trials [55]. In this study, we use secondary outcome measures related to anhedonia and other symptoms previously found to be associated with inflammation [11, 12, 14] that we believe could address some of these concerns.

Secondary outcome measures will be analyzed using biomarkers, representing the various pathways on which the n-3 fatty acids have its effect. Besides anti-inflammatory properties, n-3 fatty acids are known to exert antioxidative effects [56], hence we are planning to assess biomarkers of oxidative stress, such as F2-isoprostane, 8-OH 2-deoxyguanosine and glutathione. Other pathways associated with low-grade chronic inflammation and old age are cell aging parameters and endothelial biomarkers such as leukocyte telomere length, telomerase activity, and ICAM, VCAM [30, 31].

Furthermore, we aim to investigate potential downstream effects of low-grade inflammation such as activation of the kynurenine pathway (KP) and formation of its neuroactive metabolites. Elevated levels of TNF-α and the ratio of kynurenine/tryptophan, indicating inflammation-induced activation of the KP, have recently been found in a subgroup of depression with more severe anhedonia and poorer treatment response [57]. Lastly, also potential up-stream mechanisms, triggering inflammation, will be assessed through measuring potential proxy markers of altered gut-brain axis activity [58] and gut permeability, previously associated with depression [59]. In secondary analyzes, we also aim to investigate associations between EPA treatment response and metabolic alterations by measuring biomarkers such as leptin, adiponectin, lipids, glucose, and metabolomics.

Our study comes with several limitations, including that we have not obtained any structured information on dietary habits before and during the study. Yet, we ask subjects not to make any major changes in their eating habits. Moreover, the recruitment phase has been prolonged due to the COVID-19 pandemic and an initial lack of referrals from other health-care facilities. We have since gained much interest via ads on social media which has improved our overall recruitment procedures.

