**Discussion:**

In this study we will, for the first time using a match-mismatch trial design, test if omega-3 is an efficacious treatment for inflammatory depression. If our study is successful, it could add to the field of precision psychiatry.

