### The main aims of this trial are to test if

Add-on EPA enriched n-3 has an antidepressant effect in patients with pre-treatment hs-CRP elevations.The antidepressant effect is mediated by changes in inflammatory markers during the course of the study.The current trial design with a priori stratification using inflammatory biomarkers is feasible, which could advance “precision psychiatry”.

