## Methods

### Study design

This is a match-mismatch study with two parallel groups all receiving the same intervention. Participants are stratified according to inflammation status to a “low inflammation” or “high inflammation” group, based on high-sensitivity CRP (hs-CRP) levels before start of treatment. Participants and raters of the outcome measures are blind to group allocation during the study. Hs-CRP ≥ 3 mg/L is used to define the inflammation group based on recommendations from the Centers for Disease Control and the American Heart Association [22]. This cut-off has also been used in several depression studies to define low-grade inflammation [16, 18, 21]. Subjects will be instructed to postpone blood draw if they experience any signs of infection or sickness, and all study protocol deviations are noted. All subjects receive the same intervention of EPA 2 g/day added to their ongoing, stable medication.

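### Every participant takes EPA, so the trial cannot estimate an EPA effect in either hs-CRP group, and the between-group contrast measures differential response only under an unstated equal-course assumption

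*Protocol article*

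**What the plan says.** The Study design section of the protocol article is explicit: "This is a match-mismatch study with two parallel groups all receiving the same intervention", and "All subjects receive the same intervention of EPA 2 g/day added to their ongoing, stable medication". The groups come from a baseline measurement, with the cut at 3 mg/L: "Participants are stratified according to inflammation status to a “low inflammation” or “high inflammation” group". Under Statistical considerations, the null hypothesis is equality of means in these two groups. The mixed model has group, week and their interaction, and no term contrasts EPA with its absence.

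Four statements go further:

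- The first main aim is to test if "Add-on EPA enriched n-3 has an antidepressant effect in patients with pre-treatment hs-CRP elevations".
- The Discussion part of the abstract says the trial will "test if omega-3 is an efficacious treatment for inflammatory depression".
- The main Discussion says: "Our study will be able to inform not only about the efficacy of this particular intervention (EPA", and names inflammatory depression as the population concerned.
- The Discussion also says that the design, compared with traditional randomised trials, makes it possible "to discern whether the treatment is broadly effective in all patients or more effective in a smaller group with high inflammation".

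The limitations paragraph at the end of the Discussion covers dietary information and slow recruitment. It does not mention the absence of a comparator without EPA.

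**The concern.** An antidepressant effect, efficacy and broad effectiveness are all statements about what EPA does compared with no EPA. Nobody in this trial goes without EPA, so such statements could rest only on change from baseline. Patients enter at HAM-D-17 of at least 15, stay on their antidepressant and know that they are taking EPA, so some improvement is expected even if EPA is inert.

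The between-group contrast is better placed, but hs-CRP is a patient characteristic and was not assigned. A difference in HAM-D-17 change may reflect how hs-CRP modifies the response to EPA (a predictive role), how patients with high hs-CRP fare anyway (a prognostic role), or both. A positive result could be credited to EPA when part of it is prognosis. A null result could hide a real differential effect.

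**Working it through.** **What the contrast estimates.** Write the mean HAM-D-17 improvement in each group as the course without EPA (c) plus the EPA effect (τ):

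- high hs-CRP: c_H + τ_H
- low hs-CRP: c_L + τ_L

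The difference is (τ_H − τ_L) + (c_H − c_L). The trial observes two means for four unknowns. Neither τ_H nor τ_L can be estimated. The difference τ_H − τ_L can be estimated only if c_H = c_L. If both groups improve equally, EPA may work equally well in both or in neither, so equal improvement cannot show broad effectiveness.

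**Inputs.** From Statistical considerations: a difference of 3 points, power 0.80, alpha 0.05, a t-test, originally 45 per group and then 96 in total. The SD, the sidedness of the test and the group ratio for the 96 are not given. I assume a two-sided test and 48 per group, and solve for the SD.

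**The plan's own figures.** Because no SD is given, the sample size cannot be reproduced forward. Inverting the two-sample t-test at power 0.80 gives:

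- 45 per group: SD 5.02
- 48 per group: SD 5.19

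Both sample sizes are therefore consistent with a test of high against low hs-CRP at an SD of about 5.0 to 5.2.

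**Effect of unequal course.** The standard error is 5.19 × √(2/48) = 1.059, with 94 degrees of freedom. The noncentrality is the net difference divided by 1.059. The check at 3 points gives 3/1.059 = 2.83 and power 0.80.

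*Poorer course in inflamed patients.* A true EPA advantage of 3 points less 1.5 points of course leaves 1.5 net. The noncentrality is 1.5/1.059 = 1.42 and power is 0.29.

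*No differential EPA effect (τ_H = τ_L), but unequal course:*

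| Course difference (points) | Noncentrality | Significant in either direction | Favouring high hs-CRP if inflamed patients fare better | Favouring high hs-CRP if inflamed patients fare worse |
|---|---|---|---|---|
| 1.0 | 0.94 | 15% | about 15% | 0.2% |
| 1.5 | 1.42 | 29% | about 29% | 0.04% |
| 2.0 | 1.89 | 46% | about 46% | 0.01% |

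**Sensitivity to the group ratio.** At 32:64 with SD 5.19, the three two-sided figures are 14%, 26% and 42%. If the SD is instead back-solved at that ratio (4.90), so that power at 3 points is again 0.80, they return to 15%, 29% and 46%.

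**Evidence on course in the article.** The Discussion says that hs-CRP varies with overweight and old age and that the exclusion criteria took this into account. The Eligibility criteria admit ages 18 to 80 and list no weight limit. The Discussion also reports that inflammation-related markers "have recently been found in a subgroup of depression with more severe anhedonia and poorer treatment response". Those markers are TNF-α and the kynurenine/tryptophan ratio, not hs-CRP, and the finding concerns treatment response, not course without EPA. It makes unequal course plausible but gives no figure for it.

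**The case against.** The match-mismatch design is deliberate and openly described. The abstract's hypothesis is relative (a superior response in the inflammation group), and the null hypothesis and model match it. No within-group efficacy test is described. Patients and raters are blind to inflammation status, which limits differential expectation and rating bias. Both groups face the same HAM-D-17 threshold, so regression to the mean should largely cancel in the contrast. Background treatment must be stable for 6 weeks, and new psychotherapy is excluded.

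All of this stands, and it confines the problem to the stated aim and conclusions; the test itself suits the relative hypothesis. But blinding to inflammation status does not equalise natural course, age or weight, and does not remove expectation from within-group change. The low hs-CRP group also takes EPA, so it is a reference for differential response only under equal course.

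Three stronger readings are tempting and are not supported:

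- A reader might infer that a significant result would probably be a false positive for EPA. That requires inflamed patients to have the better course. The article's only hint points the other way, where a significant result in the hypothesised direction has a probability of 0.2% or less and the harm is lost power.
- A reader might infer that no possible result bears on the conclusions. Under equal course, the contrast does bear on whether response is greater with high inflammation.
- A reader might infer that the article expressly claims to separate prognostic from predictive roles of hs-CRP. It does not. It speaks of broad as against subgroup effectiveness, which needs that separation.

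**Conclusion.** The point holds as a mismatch between claims and design. The first aim, the efficacy statements in the abstract and the Discussion, and the claim to discern broad effectiveness all need an EPA effect that the trial cannot estimate. This part rests on no numerical assumption. The claim of greater effectiveness in the high-inflammation group can be kept only if made conditional on equal course without EPA.

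The numerical consequences are illustrations. They rest on a back-solved SD, an assumed two-sided t-test with 1:1 groups (the planned mixed model may differ in precision) and assumed course differences. Power of about 0.29 instead of 0.80 is the case that agrees in direction with the article's own hint. The 15%, 29% and 46% apply to the opposite direction. The documents settle neither direction nor size for hs-CRP.

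**What to change.** - Restate the first aim, and the efficacy statements in the abstract and the Discussion, as: *to test whether baseline hs-CRP of 3 mg/L or more is associated with a larger HAM-D-17 change during add-on EPA*.
- State that within-group change will not be reported as an antidepressant effect or as efficacy.
- In the Discussion paragraph comparing the design with traditional randomised trials, drop the claim to show broad effectiveness and the claimed advantage over those trials. Make greater effectiveness in the high-inflammation group conditional on both groups having the same course without EPA.
- Add two limitations: there is no comparator without EPA, and the contrast mixes the prognostic and predictive effects of hs-CRP.

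The cost is wording and a less favourable stated conclusion. No new patients, procedures or change to the primary test are needed.

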### Eligibility criteria

Inclusion criteria:Age 18–80 yearsDSM-5 criteria fulfilled for current unipolar depressive episode (duration of symptoms > 4 weeks)HAM-D-17 score ≥ 15CGI severity score ≥ 3Stable antidepressant or mood stabilizing treatment 6 weeks before study startSubjects agree to not significantly modify their diet during the study

Exclusion criteria:Medical illness that is serious or unstable and in the investigator's opinion could jeopardize response to treatment or interpretation of study results (e.g. malignancy, active or in remission < 1 year, insulin-dependent diabetes mellitus, active autoimmune disorder or inflammatory bowel disease)Allergy to the study compoundsCurrent infectionPregnancy or breast-feedingDiagnosed psychotic or bipolar disorder, dementia, mental retardation, or individual who lack the ability to make an informed decision due to other conditionsCurrent electroconvulsive therapyAnticoagulant treatment or known bleeding disorderCurrent, serious suicidal or homicidal risk, in the judgment of investigatorSubstance use disorder, except nicotine or caffeine, in the 3 months preceding the screening visitAny medications that could confound the biomarker analyses, within 1 week of baseline or throughout the trial, including: regular intake of non-steroidal anti-inflammatory drugs (NSAIDs) or cyclooxygenase-2 (COX-2) inhibitors, or any use of oral steroids, immunosuppressants, chemotherapy, interferon. Patients will be instructed against intake of NSAIDs (including Aspirin) or COX-2 inhibitors in the 24 h preceding a visit including biomarker assessment visitIntake of n-3 fatty acid supplementation for 3 consecutive days or more in the month preceding the screening visitInitiation of psychotherapy during the last 4 weeks or plan to start psychotherapy during the studyActive participation with ongoing study visits in other clinical studies

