### Statistical considerations

Based on the primary outcome of a difference in HAM-D-17 score between baseline and eight weeks of treatment, the minimum difference of the primary outcome we want to demonstrate is 3. In order to reject the null hypothesis that the population mean is equal between the two groups with a power of 0.80 using a T-test, we estimated, in the original sample size calculation, that 45 patients with the outcome in each group are needed (alpha = 0.05).

This is, to the best of our knowledge, the first trial of its kind. The original sample size calculation was based on information from the most similar patient group we could find with regards to the variance of the primary outcome in the intervention groups. An external statistician, not involved in any other parts of the study, conducted an interim check of the standard deviation of the primary outcome measure, and the number of subjects in each group. This was done after approximately 2/3 of the total sample had been recruited. Based on the interim check, a new sample size calculation was performed, estimating that a total of 96 subjects are needed (power = 0.8, alpha = 0.05).

The statistical model to be used to analyze our outcome measures is *mixed model repeated measures*, with patient as a random effect and treatment group, treatment week (week four or eight) and the interaction of treatment group and treatment week as fixed effects.

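### Groups are defined by hs-CRP, not by randomisation; the exclusion criteria do not cover overweight and hardly touch age, and the stated model has no covariate for either

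*Protocol article*

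**What the plan says.** **Group formation.** Study design in the protocol article states "This is a match-mismatch study with two parallel groups all receiving the same intervention", and "Participants are stratified according to inflammation status to a “low inflammation” or “high inflammation” group". The rule is a single threshold: "Hs-CRP ≥ 3 mg/L is used to define the inflammation group". There is no placebo arm and no random allocation. Patients and raters are blind to group.

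**Influences on hs-CRP.** The Discussion says of hs-CRP that "levels may be affected by a variety of factors such as overweight and old age, as well as infections", and it adds undiagnosed inflammatory processes. The next sentence is "This was taken into consideration when designing the study, specifically when defining our exclusion criteria".

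**Eligibility.** The Eligibility criteria exclude current infection, several interfering drugs and serious or unstable medical illness, with the examples "malignancy, active or in remission < 1 year, insulin-dependent diabetes mellitus, active autoimmune disorder or inflammatory bowel disease". Neither list mentions weight or BMI. The only age rule is inclusion from 18 to 80 years.

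**Model.** Statistical considerations specifies a mixed model for repeated measures with patient as random effect and "treatment group, treatment week (week four or eight) and the interaction of treatment group and treatment week as fixed effects". No covariate is listed.

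**The concern.** With no randomisation and the same treatment in both groups, the group contrast carries the whole inference. Blinding protects the ratings. It does not make the groups alike in weight or age.

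The article recognises that these two factors move hs-CRP and points to the exclusion criteria as the place where this was considered. For overweight there is nothing in that place. For age there is only an upper limit of 80, set by an inclusion criterion. The model as listed does not make up the difference.

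If weight or age is also related to change in HAM-D-17 over eight weeks, the contrast mixes that relation with any effect of inflammation. This could create a difference where inflammation plays no part, or hide one that exists. It matters most for the claims about inflammatory depression as a treatable mechanism, because those claims attribute the difference to inflammation and not merely to being above the cut-off.

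**Working it through.** **Step 1: the four named influences against the criteria.**

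| Influence named in the Discussion | Covered in Eligibility criteria or Study design? |
|---|---|
| Infections | Yes: current infection is excluded, and blood draws are postponed when the patient is unwell |
| Undiagnosed inflammatory processes | In part: known autoimmune and inflammatory bowel disease and interfering drugs are excluded |
| Old age | Barely: inclusion runs from 18 to 80 |
| Overweight | No criterion |

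The mismatch is confined to the last two rows.

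**Step 2: does the analysis cover them?** The fixed effects are group, week and group × week. The Discussion also plans secondary analyses of leptin, adiponectin, lipids and glucose, but as associations with response, not as adjustment of the group contrast. The stated limitations mention diet and recruitment, not confounding by weight or age.

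**Step 3: the SD implied by the sample size.** Statistical considerations gives a 3-point difference, power 0.80, alpha 0.05, 45 per group at first and 96 in total after the interim check. It prints no SD, so the sample sizes cannot be reproduced independently. The SD can only be solved for, assuming a two-sided test and equal groups. By the normal formula:

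SD = 3 / [(1.960 + 0.842) × √(2/n)]

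- n = 45: 3 / (2.802 × 0.2108) = 5.08 (5.02 by noncentral t)
- n = 48: 3 / (2.802 × 0.2041) = 5.25 (5.19 by noncentral t)

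I use 5.2. The sample size is not in dispute.

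**Step 4: what a given bias would do.** If no other factor is at work:

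bias = (group difference in the factor) × (its effect on HAM-D-17 change)

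Neither input is in the documents. One assumed set is a BMI gap of 5 kg/m² and a slope of 0.1 to 0.3 points per unit, giving 5 × 0.1 = 0.5 to 5 × 0.3 = 1.5 points. Another is a prevalence gap of 20 to 50 percentage points and an effect of 1 to 3 points, giving 0.2 × 1 = 0.2 to 0.5 × 3 = 1.5 points.

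Standard error of the difference = 5.2 × √(2/48) = 1.06, with 94 degrees of freedom. From the noncentral t distribution:

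| Assumed bias (points) | Share of the 3-point target | Bias / SE | Rejection rate if inflammation has no effect | Power for a true 3 points if the bias opposes it |
|---|---|---|---|---|
| 0 | 0% | 0 | 5% | 80% |
| 0.2 | 7% | 0.19 | 5.4% | 74% |
| 0.5 | 17% | 0.47 | 7.5% | 65% |
| 1.0 | 33% | 0.94 | 15.4% | 46% |
| 1.5 | 50% | 1.41 | 28.8% | 29% |

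These figures use a two-sample t-test on week-8 change as a stand-in for the mixed model. A slope of zero, which the documents do not rule out, would give no bias.

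**The case against.** **The question is partly predictive.** The Discussion asks whether a biomarker measured beforehand can tell which patients will respond. For a clinician who has only the hs-CRP value, the unadjusted difference at 3 mg/L is the right estimate. Adiposity may also act through inflammation, and adjustment would then remove part of what is being studied. This stands. It is why the unadjusted model should be kept and not replaced. It does not answer the mechanistic aim, which concerns inflammation itself.

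**The sentence is softer than a claim of control.** A reader might infer that the article says overweight and age were dealt with by exclusion. It says only that the influences were considered when the criteria were set, and for infection and inflammatory disease the criteria bear this out. This stands too, and it narrows the fault to one sentence that is inaccurate for two of four factors.

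**An adjusted analysis may be planned elsewhere.** A full protocol or SAP is not shown, and silence in an article proves nothing. A reader should not conclude that no adjusted analysis exists. What can be said is that the article lists its fixed effects explicitly and refers weight and age to criteria that do not contain them.

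**Confounding needs two links.** The Discussion links overweight and age to hs-CRP, not to change in HAM-D-17. A reader might picture leaner, younger patients set against heavier, older ones, but no baseline data are given. That contrast is an expectation, not an observed imbalance.

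**Conclusion.** The point holds in limited form and should be fixed; it does not invalidate the trial. The groups are not randomised, the article names overweight and old age as influences on hs-CRP, the criteria it refers to do not cover the first and hardly touch the second, and the listed model has no covariate for either. As stated, the analysis can show whether patients above the cut-off change differently. It cannot show whether inflammation, as opposed to weight or age, accounts for the difference.

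The size and direction of any bias cannot be derived from the documents. The 7.5–29% false-positive range depends on an assumed bias of 0.5 to 1.5 points, an assumed 48:48 split, a two-sided test and an SD solved from the sample size. A bias of 0.2 points would be negligible (5.4%).

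The stronger conclusion, that the adjusted estimate must become the sole basis for saying that inflammation status predicts change, is not supported: the article also poses a predictive question, and the unadjusted estimate answers it.

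**What to change.** 1. **Keep the unadjusted model** for the question whether hs-CRP status predicts change in HAM-D-17.
2. **Pre-specify beside it the same model with age, BMI and sex as covariates**, before outcome data are analysed by group. Sex is a conventional addition; the documents do not name it as an influence on hs-CRP.
3. **State the rule of interpretation.** Attributing a difference to inflammation itself requires the adjusted estimate to agree with the unadjusted one. Define agreement in advance by direction, size and confidence interval, since the sample size was not set for the adjusted model.
4. **Report age, BMI and sex at baseline by group.**
5. **Correct the Discussion sentence** to say that the exclusion criteria address infection and inflammatory disease, while weight and age are examined by adjustment.

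**Cost.** Three covariates use 3 of about 94 degrees of freedom. Height and weight are needed for each patient if not already recorded. The adjusted interval will be wider to the extent that the covariates are correlated with group, and the adjusted estimate will be conservative if adiposity acts through inflammation, which is why both are shown. Recruitment, treatment and the visit schedule do not change.
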